## **9.2 Serious adverse events after A(H1N1)v vaccination**

All SAEs following A(H1N1)v vaccination of the participants of the total study cohort reported to the AEFI register during the clinical follow-up and 6 months thereafter, as well as SAEs reported by the participants of the immunogenicity cohort within 6 months after the last vaccination will be collected. When the investigator and/or designate becomes aware of a SAE, all relevant available documentation (e.g., hospital progress notes, laboratory, and diagnostics reports) relative to the event will be reviewed and all relevant information will be recorded in the study database. The investigator and/or designate will attempt to establish a diagnosis of the event based on signs, symptoms, and/or other clinical information. In such cases, the diagnosis will be documented as the SAE and not the individual signs/symptoms.

## **9.3 Assessment of causality**

The investigator and/or designate will assess the relationship between the A(H1N1)v vaccination and the occurrence of each SAE defined in chapter 9.1. Alternative causes, such as natural history of the underlying diseases, concomitant therapy, other risk factors and the temporal relationship of the event to the vaccination will be considered and investigated. The investigator and/or designate will follow the recommendations of WHO, in the determination of his/her assessment.

SAEs will be examined by the investigator and/or designate to the extent to be able to determine all contributing factors applicable. Other possible contributors may include e.g. medical history, other medication, protocol required procedure, other procedure not required by the protocol, lack of efficacy of the vaccine, erroneous administration or other cause.

The causal relationship between the A/H1N1 vaccination and the event will be assessed as

- unrelated; the causal relation is not plausible and/or there is another clear cause for the event

- unlikely; the causal relationship can not be ruled out, but there is another, more probable cause for the event
- possible; the causal relationship is possible, but there is another, equally probable cause for the event
- probable; causality is plausible and there is no other as probable cause for the event

#### **9.4 Follow-up of serious adverse events and assessment of outcome**

After identifying SAEs defined in chapter 9.2 the investigator and/or designate will follow up each subject until the event has resolved, subsided, stabilised, disappeared, the event is otherwise explained, or the subject is lost to follow-up. Relevant additional information will be updated in the study database.

#### **9.5 Treatment of serious adverse events**

Treatment of any SAE or other adverse events of the study participants is at the sole discretion of the physician responsible for the person's medical care and according to current good medical practice.

#### **9.6 Regulatory reporting requirements for serious adverse events**

According to the national legislation, THL will report to the National Agency of Medicines and the ethics committee of PSHP all SAE cases defined in chapter 9.2. for which the causal relationship with the A(H1N1)v vaccine can not be ruled out and which are unexpected according to the investigator's brochure within time limits defined in the regulation of the National Agency of Medicines (LL Dnro 2740/0.5.1./2007 ). Once a year, THL will provide the National Agency for Medicines and the ethics committee of PSHP with a list of all SAE cases defined in chapter 9.2. with potential causal relationship to the A(H1N1)v vaccine which have occurred to the participants of the effectiveness cohort during the SAE detecting period, defined to end 6 months after the end of the clinical follow up of the total study cohort, and for the events reported by the participants of the immunogenicity cohort, when 6 months has elapsed since the date of the last vaccination.

The occurrence of serious adverse events and AESI recognised in the register data collected from the health care data systems of Tampere city and TAUH is a result variable of this large cohort study. Recognising, analysing and reporting individual SAE cases from register data only or analysing suspected cases will not be possible in the limits of resources of this study. Summaries of adverse reactions relating to these safety result variables will be supplied to the National Agency for Medicines and ethics committee in the study report.

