### **2.2 Secondary objectives**

- To assess the safety for 6 months after vaccination with the A(H1N1)v vaccine during the follow up;
- To determine humoral and cellular immune responses to one or two doses of the A(H1N1)v vaccine in 200 adults aged 18 to 75 years
- To evaluate the incidence, severity and possible complications of laboratory-confirmed infection with the novel A(H1N1)v influenza virus;
- To explore the effectiveness of the A(H1N1)v vaccine in subgroups stratified by age

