## 9 Serious adverse events (SAE) reporting

### 9.1 Definition of SAE

An adverse event is any untoward medical occurrence in a patient or clinical investigation subject administered a pharmaceutical product and which does not necessarily have a causal relationship with this treatment. An adverse event (AE) can therefore be any unfavourable and unintended sign (including an abnormal laboratory finding), symptom, or disease temporally associated with the use of a medicinal product, whether or not related to the medicinal product.

An adverse event is defined as 'serious' when it meets one of the following criteria:

1. results in death,
2. is life-threatening,
  - The term 'life-threatening' in the definition of 'serious' refers to an event in which the subject was at risk of death at the time of the event. It does not refer to an event which hypothetically might have caused death, if it were more severe.
3. requires hospitalisation or prolongation of existing hospitalisation,
  - Hospitalisation signifies that the subject has been detained (or involving at least an overnight stay) at the hospital or emergency ward for observation and/or treatment that would not have been appropriate in the physician's office or outpatient setting. If a complication that occur during hospitalisation prolongs hospitalisation or fulfils any other serious criteria, the event is serious. When in doubt as to whether hospitalisation occurred or was necessary, the event should be considered serious. Hospitalisation for elective treatment of a pre-existing condition that did not worsen from baseline is not considered a SAE.
4. results in persistent or significant disability/incapacity
5. is a congenital anomaly/birth defect in the offspring of a study subject.

In addition, medical or scientific judgement will be exercised in deciding whether an adverse event is serious in other situations. Important medical events that may not be immediately life-threatening or result in death or hospitalisation but may jeopardize the subject or may require medical or surgical intervention to prevent one of the other outcomes listed in the above definition, will also be considered serious. Examples of such events are invasive or malignant cancers, intensive treatment in an emergency

room or at home for allergic bronchospasm, blood dyscrasias or convulsions that do not result in hospitalisation.

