### **11.2 Sample size considerations**

Based on recent questionnaire data from Finland, as part of FLUMODCONT (pandemic FLU MODelling CONTainment strategies),project, the assumption is that, if offered the vaccine, 90% will take it. Hence the expected number of unvaccinated persons in the study cohort is 400. Furthermore, it is assumed that during the first wave of the A(H1N1)v pandemic, which is the planned period of follow-up in this study, 20% of the unvaccinated become infected by the A(H1N1)v virus, i.e. 80 expected cases. The assumed effectiveness of the vaccine is 70%. The study is

powered to demonstrate the effectiveness of the vaccine such that the lower level of the 95% confidence interval is above 50%, which is regarded as the level of clinical relevance for the A(H1N1)v vaccine. With a random sample size of 4,000 the power of the study is 95%. High power for the effectiveness evaluation is preferred, since taking into account potential confounders, as well as possible unbalance in the age distribution of the study cohort (see Section 3) will lower the power.

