### **11.3 Statistical methods for analyses**

The incidence of the laboratory-confirmed H1N1 pandemic influenza will be calculated as the number of cases divided by the person-time at risk, where person-time at risk is defined as compliance to the regular contacts. Periodic variation of incidence in calendar time will also be explored both in vaccinated and unvaccinated groups. Event-history analysis methods will be used for the evaluation of the effectiveness of the vaccine, where the risk of acquiring A(H1N1)v-influenza will be compared between the vaccinated/unvaccinated states, by accounting for calendar time and other potential confounders. Vaccine effectiveness will be calculated as 1- relative risk. For the vaccine adverse events, case-series method will be used for comparing the incidences between risk and non-risk periods. Descriptive analysis will be conducted for the immunogenicity cohort, such as calculation of geometric mean titres and percentages over pre-defined thresholds. Due to the nature of the study (see Section 3), other descriptive analyses and tests of hypotheses may also be carried out but the choice of subsequent hypotheses will be data dependent

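### Post-vaccination influenza events count both as severity outcomes and as register safety events, and the case series names no way to separate them, so its relative incidence can be biased in either direction

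*Protocol*

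**What the plan says.** **Severity.** Protocol 2.2 sets a secondary objective on the incidence, "severity and possible complications of laboratory-confirmed infection with the novel A(H1N1)v influenza virus". Section 8.1.1 draws this from the Tampere city and TAUH records of confirmed cases.

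**Safety.** Section 8.3.2 takes safety outcomes from the records of the Tampere health centre, the city hospital and TAUH, including hospitalisations, emergency visits and deaths. In 9.1 an adverse event counts whether or not the product caused it, and it is serious if, among other criteria, it "requires hospitalisation or prolongation of existing hospitalisation". The only admission excluded is elective treatment of a pre-existing condition that has not worsened. The AESI list in 8.3.1 includes convulsions, encephalitis and vaccination failures.

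**Review of register events.** Section 9.6 names "The occurrence of serious adverse events and AESI recognised in the register data collected from the health care data systems" of Tampere city and TAUH as a result variable. It adds that recognising or analysing individual SAEs from register data alone is beyond the study's resources.

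**Analysis.** For vaccine adverse events, section 11.3 says the "case-series method will be used for comparing the incidences between risk and non-risk periods". It mentions calendar time and other confounders only for effectiveness.

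**Planning figures.** In 11.2, "the assumption is that, if offered the vaccine, 90% will take it". It continues: "Hence the expected number of unvaccinated persons in the study cohort is 400", and "20% of the unvaccinated become infected by the A(H1N1)v virus, i.e. 80 expected cases". Finally, "The assumed effectiveness of the vaccine is 70" per cent.

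**The concern.** The vaccine is meant to prevent A(H1N1)v disease. If that disease also counts as a safety event, part of the safety result measures effectiveness and epidemic timing rather than harm.

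A case series controls for characteristics of a person that stay fixed. It does not by itself control for a cause that changes over time. Infection risk changes with the wave and, on the plan's own assumption, with vaccination.

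At stake is the reading of the register-based safety result for endpoints that influenza can cause. A vaccine-caused excess could be diluted, or an apparent excess could arise where there is none.

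**Working it through.** **Step 1. Does the overlap follow from the text?** Take a participant admitted with confirmed A(H1N1)v influenza after the first dose.
- Under 2.2 and 8.1.1 the admission is a severity outcome.
- Under 9.1 it is an SAE, because cause is irrelevant and influenza is not excluded. Under 9.6 it enters the register result variable.
- Under 5.3 the person is vaccinated from the first dose, however recent. On a natural reading the case is then also a vaccination failure, hence an AESI under 8.3.1.
- Section 9.3 calls for alternative causes to be weighed. However, 9.2 collects SAEs from the AEFI register and the immunogenicity participants, and 9.6 rules out individual work on register-only events. For those events influenza is not removed as a cause.

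**Step 2. The plan's own figures.** Unvaccinated: 4,000 × 0.10 = 400, and 400 × 0.20 = 80 cases, as 11.2 states. Vaccinated: 4,000 × 0.90 = 3,600, and 3,600 × 0.20 × (1 − 0.70) = 216 expected infections. This is approximate, since it treats them as vaccinated throughout the wave. If each counted as a vaccination failure, there would be about 216 events on a list of otherwise mostly specific diagnoses. A vaccination failure also cannot occur before vaccination, so any pre-vaccination non-risk time contains none by definition. The 95% power in 11.2 concerns effectiveness and is not affected. The protocol gives no corresponding figure for safety.

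**Step 3. How mixing moves the estimate.** Let
- f = share of non-risk-period events caused by A(H1N1)v infection (not in the documents; assumed 10%, 30%, 50%);
- R = true relative incidence for all other causes (assumed 1 or 2);
- k = relative incidence of infection-caused events, risk versus non-risk time.

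Observed relative incidence = (1 − f) × R + f × k.

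Section 11.3 fixes no windows. Three placements, each with equal infection pressure in both periods and 70% effectiveness once protected, give:

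| Placement | k | R = 2, f = 10 / 30 / 50% | R = 1, f = 10 / 30 / 50% |
|---|---|---|---|
| (a) Non-risk time before vaccination, risk window protected | 0.3 | 1.83 / 1.49 / 1.15 | 0.93 / 0.79 / 0.65 |
| (b) Non-risk time before vaccination, risk window not yet protected | 1 | 1.90 / 1.70 / 1.50 | 1.00 / 1.00 / 1.00 |
| (c) Non-risk time later and protected, risk window not yet protected | 1/0.3 = 3.33 | 2.13 / 2.40 / 2.67 | 1.23 / 1.70 / 2.17 |

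Examples at f = 30%, R = 2: (a) 0.7 × 2 + 0.3 × 0.3 = 1.49; (c) 0.7 × 2 + 0.3/0.3 = 2.40. In (a) a true value of 2 is fully cancelled when f = (2 − 1)/(2 − 0.3) = 59%.

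**Step 4. The wave.** If infection pressure in the risk window is w times that in non-risk time, k is multiplied by w. The estimate falls below R when k is less than R and rises above it when k exceeds R. In placement (a) with R = 1, the direction reverses once 0.3 × w > 1, that is, w above 3.33.

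**Step 5. Limits.** For an AESI that influenza rarely causes, f is near zero and the observed value is close to R.

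**The case against.** **The overlap is inferred.** Section 11.1 places the safety endpoints in 8.3, and 8.3.1 speaks of serious (unexpected) adverse reactions, not all SAEs. No sentence says influenza admissions enter the case series. This is fair: the overlap has to be read from several sections together. But 9.6 makes register SAEs and AESI a result variable, and without case-level review nothing tells a reaction from an unrelated event. Vaccination failures are listed outright.

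**The direction is open.** A reader might infer that the mixing hides a harm, because a working vaccine lowers influenza events after the dose. The documents do not support that as the general result. Section 11.3 contrasts risk with non-risk periods; it does not say before versus after vaccination, nor vaccinated versus unvaccinated persons. Section 15 extends register follow-up to 6 months after clinical follow-up ends, so much non-risk time may fall after the dose. Section 8.2 first measures the immune response at 4 weeks, so an early risk window may be largely unprotected. This objection stands in full.

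**The size is not anchored.** Section 11.2 gives infections, not admissions, so f is unknown and differs by diagnosis. This also stands.

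**Windows and covariates belong in the SAP.** Largely true, and the SAP is not shown. Section 8.3.2 also allows record review if needed, and 8.3.1 allows the list to be adapted. However, the SAE definition, the AESI list and the decision against individual review are fixed in the protocol.

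**Removing events can itself mislead.** Dropping every event soon after an infection conditions on something vaccination changes, and could discard a vaccine-caused event. This stands and shapes the fix.

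**Conclusion.** The point holds as a possible bias of unknown sign and size. By the protocol's own definitions, post-vaccination influenza events are both severity and safety outcomes, and neither case review nor any adjustment named for the case series separates them. It matters for endpoints that influenza can cause: all-cause SAEs, convulsions and encephalitis. It also matters for vaccination failures, for which a comparison with pre-vaccination time is meaningless.

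The figures above are illustrations. With f from 10% to 50%, a true value of 2 appears as 1.15 to 2.67 and a true value of 1 as 0.65 to 2.17, depending on the placement. They rest on assumed f and R, the plan's 70% effectiveness and equal infection pressure in both periods. The documents do not allow an estimate of the actual bias. They also do not support a reading that the whole safety evaluation is compromised, since AESI that influenza rarely causes are little affected. The change is worth making because it is cheap and the data are already being collected.

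**What to change.** In 8.3.1 and 11.3:

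1. Report vaccination failures and influenza-coded events under effectiveness and severity, and leave them out of the case series. Keep them listed as AESI for reporting, since the list is adapted from regulatory recommendations.
2. For the remaining SAEs and AESI, adjust the case series for calendar time and fit laboratory-confirmed A(H1N1)v infection as a second time-varying exposure. The dates are available from 8.1 and 8.1.1.
3. Show results with and without infection-linked events, so that exclusion is never the only analysis.

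The cost is protocol and analysis wording, one linkage of data already held and slightly more analysis work. The restricted version will have fewer events. Infections that were never tested remain mixed in, so some bias may persist.

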## **10 Laboratory procedures**

### **10.1 Laboratory methods for assessing the immunogenicity of the A(H1N1)v vaccine**

Blood specimens for assessing immunogenicity of the A(H1N1)v vaccine will be processed for white blood cell isolation (from 50 ml of blood) and obtaining serum specimens (from 10 ml of blood). The samples for cellular immunity assays will be sent to the Virus Infection Unit (ROVI) of THL, Department of Vaccination, where the peripheral blood mononuclear cells (PBMC) will be isolated and stored at -130 °C or colder, and cell-mediated immune responses will be analyzed simultaneously for all 3-5 specimens obtained from the same subject according to the instructions of ROVI. Serum specimens will be stored at -20 °C or colder and humoral immune responses will also be analyzed for all 3-5 specimens simultaneously.

Humoral immunity against the vaccine virus (likely A/California/7/2009 H1N1v or equivalent) will be studied using standard hemagglutination inhibition (HI) and neutralization (NT) tests (6). Study viruses include the wild type virus that is used for the vaccine for studying the homologous response and most recent swine-origin lineage viruses that have been isolated in the fall 2009 as well as other recent H1N1 (Brisbane/59-like viruses) and H3N2 (Brisbane/10-like viruses) viruses. All viruses required for antibody determination are either already available or will be obtained (new influenza A(H1N1)v isolates) prior to the study.

## **10.2 Laboratory methods for identifying of laboratory-confirmed influenza A(H1N1)v cases**

### **10.2.1 Nasal and throat swab samples**

Viruses are intracellular pathogens. In order to obtain a good diagnostic sample for viral studies it must be attempted to collect as many epithelial cells as possible from the nostrils and the throat without causing excessive discomfort to the patient. To achieve maximal sensitivity, both nostrils and the throat must be swabbed. Nasal and throat swab specimens will be obtained from individuals within 5 days after onset of ILI symptoms defined in chapter 5.1.

To obtain the nasal sample, a preferably flocked swab will be inserted approximately 3 – 4 cm into the first nostril, left in place for a few seconds, then slowly withdrawn with a rotating motion in order to trap as many epithelial cells as possible. If possible, the same swab will be used to sample also the other nostril. The swab will be broken into the tube containing transport medium. The throat, the tonsils, the uvula, and the posterior wall of the pharynx will be sampled using a fresh swab. This swab will be broken into the same tube containing the nasal swab. The sample will be placed in a refrigerator (temperature 4° C) for short-term storage (24 – 48 hours), and/or in a freezer ( $\leq -60^{\circ}$  C) for extended storage until analysed. If needed, the samples will be sent to the laboratory by overnight mail in a small styrofoam box containing cool-cushions.

In ROVI, A(H1N1)v influenza viruses identified by reverse transcription polymerase chain reaction (RT-PCR) method and, if needed, virus culture. For differential diagnostics and potential assessment for associations, influenza A and B as well as respiratory syncytial virus and other viruses causing respiratory will be identified from the combined nasal-throat swab specimens. Furthermore, typing and subtyping may be performed using instructions of ROVI. Resistance to oseltamivir may be determined from selected samples.

RT-PCR methods for detecting influenza A (and B) virus-specific RNAs are readily available in the laboratory. Virus Infection Unit at THL functions as a National Influenza Center (NIC) and the unit carries out national surveillance work for the identification of circulating influenza virus strains in Finland. Approximately 1,000 nasopharyngeal specimens/year are screened and 150-200 influenza viruses identified and cultured

each year. Influenza A virus-specific RT-PCR is based on general identification of influenza A viruses by matrix (M1) gene-specific primers that identify all influenza A viruses independent of their H or N gene subtype. Virus Infection Unit has also developed swine-origin pandemic influenza A(H1N1)v specific RT-PCR assay based on H1 and NS1 gene specific primers that reliably enable the detection of swine-origin A(H1N1)v virus infections. The assay was successfully used to determine the first influenza A(H1N1)v infection cases in Finland in early May, 2009. Thus the methodology for the rapid and specific influenza A virus diagnostics, for isolation and further characterization of influenza viruses are well established in the laboratory.

### **10.2.2 Blood samples for additional information on laboratory-confirmed A(H1N1)v influenzawab samples**

Of blood samples (á 10 ml) obtained at acute and convalescent phases of ILI, serum specimens will be prepared and stored at -20 °C or colder until analysed. The antibody titers will be measured using standard hemagglutination inhibition and neutralization tests (6).

